#### Health economic appraisal of hypnosis preparation for childbirth in late pregnancy

Antenatal hypnosis preparation for childbirth may be associated with substantial decreased costs to the health care system and an economic appraisal has been incorporated into the trial from its inception with a view to running a concurrent side study to the main trial. The magnitude of the marginal direct cost of providing the group hypnosis sessions is expected to be low in relation to the total costs of an episode of care. A cost effectiveness analysis is planned that will compare the opportunity cost to society of the additional resources required for the proposed intervention with the consequent gain in health outcome. Direct and indirect costs will be considered including those incurred by the health service, mothers and their immediate families as determined by surveying a subset of trial participants. Resource items will be quantified from the medical record and patient interview. Outcomes such as postpartum hospital readmission within six weeks of discharge; duration of postpartum hospital stay; cost of hospital stay; hospital follow up for long-term morbidity will be calculated.

#### Safety concerns

Women scoring > 12 on Edinburgh Post Natal Depression Score, or where otherwise indicated will be advised by a researcher to see their GP for advice. All participants have consented for treating clinicians to be informed of any clinical concerns and the need for further clinical assessments during the trial.

#### Confidentiality and data security

All patient data will be de-identified during analyses. All trial documentation and participant identifiers will be kept in a locked cabinet and stored for 15 years after publication of the trial results. Trial data on a computer database will be kept password protected.

## Discussion

This trial seeks to determine the efficacy or otherwise of antenatal group hypnosis preparation for childbirth in late pregnancy.

### Evidence for scale validity

#### Measuring pain

Pain is not a directly observable or measurable phenomenon, but rather a subjective experience with sensory and affective elements [65]. In this sense, pain is a psychological phenomenon. Measuring analgesia requirements during labour is a well recognised reliable near objective measure of pain and is commonly used as a *post hoc *measure of pain [7].

#### Psychological testing in pregnancy

The main psychological measures that we plan to use are well-established, validated scales that have been recommended for child-bearing women [36,66]. The Edinburgh Postnatal Depression (EPDS)[61] and the Spielberger anxiety scale[60] will be administered, before the allocated treatments antenatally and in the post-natal period, by researchers blinded to group allocation. The EPDS has been developed to assist primary care health professionals to detect mothers suffering from postnatal depression; a distressing disorder more prolonged than the "blues" (which occur in the first week after delivery) but less severe than puerperal psychosis. Previous studies have shown that postnatal depression affects at least 13% of women and that many depressed mothers remain untreated. These mothers may cope with their baby and with household tasks, but their enjoyment of life is seriously affected and it is possible that there are long-term effects on the family. The EPDS was developed at health centers in Livingston and Edinburgh in the UK. It consists of ten short statements. The mother underlines, which of the four possible responses is closest to how she has been feeling during the past week. Most mothers complete the scale without difficulty in less than 5 minutes. The mother completes the scale herself, unless she has limited English or has difficulty with reading. An EPDS > 12 is considered the level where a need for intervention is clinically indicated [61,67]. The validation study showed that 92.3% mothers who scored above this threshold were likely to be suffering from a depressive illness of varying severity. Other planned measures of "Satisfaction" and "Maternal control" have been utilised previously in pregnancy using Likert scales or visual analogue scores(VAS) [68].

#### Hypnotisability testing

In the laboratory, approximately 14% of people are refractory or uncooperative towards hypnosis, about 36% enter a light hypnotic state, over 25% perform in the moderate range and just under 25% score as highly responsive69 Hypnotisability tests used for research purposes tend to be extensive, can take up to an hour to administer and require a hypnosis induction [70]. Awake suggestibility tests allow for hypnotisability testing of all groups without subjecting women in non-hypnosis groups to a hypnosis induction which may in itself have an effect on our outcomes of interest. The creative imagination scale[62] can be used to test for hypnotisability without a hypnotic induction and has been validated in pregnancy [36]. The administration and scoring of this scale takes approximately 20 minutes to perform. In the clinical setting of stress and pregnancy responsiveness of subjects to hypnosis appears to increase dramatically [71].

#### Blinding

The nature of the intervention makes it difficult to double blind comparisons between hypnosis groups and non intervention controls. However every attempt will be made to conceal treatment allocations from obstetricians, anaesthetists, midwives and those personnel collecting and analysing data. All participants will be informed that they may or may not appreciate which group they are in. Women allocated to usual care will probably realise they are not in an intervention group. Although it may not be possible to blind the administration of our intervention, all data will be collected and analysed by researchers who will be unaware of the participant's group allocation. Any comparisons of participants receiving an intervention in Groups 1 and 2 will be in a true double blind fashion with both participants and outcome assessors blinded to allocation. Our primary outcomes and key secondary outcomes are designed to be as objective as they can be for a study of this type. An assessment of blinding will be determined by asking participants if they thought they were in a control or intervention group in the final post-partum questionnaire.

There are four main reasons that provide the rationale for a clinical hypnosis study in late pregnancy. Firstly, pain and the fear of pain associated with childbirth is nearly universal and currently utilised pharmacological methods of pain relief have limitations and well recognised complications associated with their use. Confirming the association of reducing pharmacological analgesia requirements in labour will reduce the incidence of their complications and potentially improve the childbirth experience. Hypnosis has been shown to effectively provide anxiolysis and analgesia in a range of clinical[28,72,73] and laboratory settings [30,39,69,74]. Secondly, we have found that our hypnosis intervention is easy to administer and appears to be a relatively simple and inexpensive means of preparing women for labour and childbirth. Hypnosis has a long history of use in childbirth which is claimed to be one of the most useful settings in which to utilise hypnosis [23,75,76]. Systematic reviews of the evidence to date[10,22,43] and our use of hypnosis as antenatal preparation for labour[47,77] suggest benefits in: reducing analgesia requirements; reducing the incidence of oxytocin administration; and increasing the incidence of spontaneous vaginal birth. However the existing evidence from small or poorly designed trials is still inadequate to confirm these effects. Renewed interest in this topic and the call for more research is as relevant today as it was 30 years ago [78]. Third, this is the first randomised trial investigating the effects of antenatal hypnosis preparation for childbirth in late pregnancy in both nulliparous and multiparous women; with a structured defined intervention that is easily reproducible and has excellent external validity; with clearly described adequate allocation concealment; and with the incidence of postnatal depression as a key endpoint. Fourth, peri-operatively the use of hypnosis has been shown to increase the incidence of beneficial outcomes and lower costs. This is likely to be translated into the childbirth setting.

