### Additional specific aims

6. To compare two methods of delivering antenatal group hypnosis in a double blind fashion, one method using a hypnotherapist to deliver the intervention followed by an audio cd on hypnosis for re-enforcement of the techniques learned. The other method is to use the an audio cd on hypnosis alone administered by a nurse with no hypnotherapy training.

**[see **Additional file 1**] **for detailed hypotheses

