### Group 1: Antenatal hypnosis plus hypnosis audio CD (hypnotherapist guided)

#### Session 1

Discussion about fears and anxieties. Questions about hypnosis answered, Seeding expectancy of success. Basic hypnosis taught using progressive relaxation with a self hypnosis component at the end. Session 1 cd played and women asked to practice this on a daily basis until the next session.

#### Session 2

After a hypnosis induction, suggestions are given for confidence, coping and strength during contractions. Women are asked to focus on breathing for analgesia and relaxation. Suggestions for time distortion: this allows contractions to seem shorter and rest periods between contractions longer than they really are. Standardised suggestions given for a labour rehearsal involving recurrent fractionation and staircase imagery[21]. Session 2 section of cd played and women asked to practice this on a daily basis until the next session.

#### Session 3

Pain control techniques – Amnesia suggestion for unhelpful comments and utilisation of helpful suggestions. Dissociation and lower body anaesthesia elicited using the lignocaine spa imagery21 Suggestions for uterine contraction after delivery and relaxation to facilitate breastfeeding. Session 3 audio cd played and women asked to practice hypnosis while listening to the whole cd on a daily basis until the birth. Women told that they can listen to the labour audio cd during labour if they wish.

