### Group 2: Antenatal hypnosis audio CD (nurse guided)

#### Session 1

Structured information given regarding getting the most from the cds. An explanation is given regarding the structure of the sessions and how to obtain most benefit when listening to the cd. It is suggested not to try to pay conscious attention and to go along with any instructions given will provide optimum benefit. Questions answered and Session 1 audio cd played. Participants are asked to listen to the cd on at least a daily basis until the next session.

#### Session 2

Questions answered. Session 2 audio cd played. Participants are asked to listen to the cd on at least a daily basis until the next session.

#### Session 3

Questions answered. Session 3 audio cd played. Participants are asked to listen to the cd on at least a daily basis until the next session.

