### Data collection and outcomes

Our primary outcome the use of pharmacological analgesia during labour and childbirth will be collected from the birth register where all analgesia is documented by the attending midwife. Any unclear entries will be clarified by referring to the medical and midwifery record of the birth. Most of our key secondary endpoints such as the use of oxytocics, the mode of delivery, neonatal Apgar score at 5 minutes < 7 and maternal admission to the High Dependency Unit (HDU) or the Intensive Care Unit (ICU) will be obtained from the birth register. These outcomes will have been documented by the attending midwife who will be unaware of the parturient's group allocation. A second researcher who is blinded to treatment allocation will manage data collections on the ward and from post-natal questionnaires. Details of maternal side effects will be collected such as; PPH=>600 mls; blood transfusion; death; ICU admission, meconium stained liquor; babies admitted to neonatal unit. Mothers will be asked to complete a postpartum questionnaire while in hospital and asked to rate the overall pain experienced during labour and childbirth, whether the birth experience was: Worse/better/same as expected, whether they felt in control during the labour during the birth and whether the birth was rated a positive or negative experience. We will also ask: how well the mother felt she coped with labour and childbirth; whether hypnosis training was obtained outside the trial; and whether hypnosis will be used in future pregnancies. Length of neonatal nursery stay, length of maternal stay in hospital and the number of women breast feeding at discharge from hospital will also be recorded.

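### The Group 1 v Group 2 comparison is labelled double blind although women can see which method they received; the blinding check cannot support the label, and the statements on the midwife's awareness disagree

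*Protocol article*

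**What the plan says.** On the two hypnosis arms, aim 6 (Additional specific aims) is "To compare two methods of delivering antenatal group hypnosis in a double blind fashion". The Blinding section says that comparisons of Groups 1 and 2 "will be in a true double blind fashion with both participants and outcome assessors blinded to allocation". The same section concedes that hypnosis against usual care is hard to double blind, that control women will probably realise their status, and that blinding the administration may not be possible. Its check of blinding consists of "asking participants if they thought they were in a control or intervention group in the final post-partum questionnaire".

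On the midwife, the Data collection and outcomes section says that the primary outcome "will be collected from the birth register where all analgesia is documented by the attending midwife", and that the key secondary outcomes will have been "documented by the attending midwife who will be unaware of the" woman's allocation. The Abstract likewise presents concealment from midwives as achieved. The Blinding section says only that "every attempt will be made to conceal treatment allocations from obstetricians, anaesthetists, midwives" and from data staff.

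On the labour CD, the section on developing the audio CDs describes a fourth CD made for use in labour and ties it to no arm. Session 3 for Group 1 adds: "Women told that they can listen to the labour audio cd during labour if they wish". Session 3 for Group 2 does not mention it and reads: "Session 3 audio cd played. Participants are asked to listen to the cd on at least a daily basis until the next session".

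**The concern.** A reader of the trial report will take a double-blind label to mean that the woman did not know what she received. If the described sessions make that impossible, aim 6 is reported with a protection that the design lacks. This matters most for outcomes that the woman rates herself, including the postnatal depression score, which the closing rationale of the Discussion calls a key endpoint.

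The midwife matters for a different comparison. She attends the labour and documents the analgesia that forms the primary outcome. If she hears a hypnosis recording, she knows that the woman is not in usual care. An unqualified statement that she is unaware would then be wrong for some births in the main contrast.

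**Working it through.** No figure in the plan is in dispute, so the check sets the sections side by side.

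**1. Can a woman tell which method she received?**

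| | Group 1 | Group 2 |
|---|---|---|
| Leader | qualified hypnotherapist | nurse without hypnotherapy training |
| Session 1 | talk about fears, hypnosis taught live, then CD | advice on using the CDs, questions, CD |
| Session 2 | live induction and suggestions, then CD | questions, CD |
| Session 3 | live pain-control techniques, then CD | questions, CD |

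The difference is visible from attending. The section on interventions and comparisons also says that women hear before consent of a 66% chance of one of the hypnosis interventions, so they know that more than one exists. Blinding to allocation does not hold for a participant who attends.

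**2. Which outcomes does this reach?** The mother normally completes the EPDS herself, and she rates her own pain, control, coping and birth experience. The section on psychological testing says that blinded researchers administer the EPDS and anxiety scales. That blinds the person handing over the form, not the person answering it. For these outcomes the assessor is the participant, so in Group 1 v Group 2 they are not assessed blind.

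**3. What can the blinding check show?** The answers offered are control or intervention, and both hypnosis arms are interventions:

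- A woman who knows exactly which method she had is expected to answer intervention.
- A woman who knows only that she had some form of hypnosis is expected to answer intervention.

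The two states of knowledge give the same expected answer. A high rate of that answer in both arms fits full awareness of the method as well as none, so it is no evidence for blinding between Groups 1 and 2. Midwives are not asked.

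**4. The midwife.** One section states unawareness as fact, another promises an attempt. A labour CD exists, and at least Group 1 women are told that they may play it. If it is played, it reveals hypnosis v usual care to the person recording the primary outcome. It separates Group 1 from Group 2 only if one of them lacks it, which the article does not establish.

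**5. Scale, as an illustration only.** The document gives no bias size, so the shifts below are assumptions. Inputs from the power calculation are n = 135 per group, two-sided 0.05, and rates of 80% and 64%. The 135 reproduces with a continuity correction (123 without), and 135 / 0.90 = 150. Suppose there is no true effect, but awareness alone moves analgesia use from p1 to p2 = p1 − d. With p̄ = (p1 + p2)/2,

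s0 = √[2p̄(1 − p̄)/n], s1 = √[(p1(1 − p1) + p2(1 − p2))/n],

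false-positive rate = Φ((d − 1.96·s0)/s1) + Φ((−d − 1.96·s0)/s1).

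For p1 = 0.80 and d = 0.05: s0 = 0.0508, s1 = 0.0507, and the rate is 0.164 + 0.002 = 0.166.

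| Assumed shift d (points) | 0 | 3 | 5 | 8 | 10 |
|---|---|---|---|---|---|
| From 80% | 5% | 9% | 17% | 34% | 48% |
| From 64% | 5% | 8% | 13% | 27% | 39% |

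This shows what a given shift would do. It is not evidence that any shift occurs.

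**The case against.** The strongest defence is that women may not know which delivery method is expected to do better, and that they are told they may or may not recognise their group. That is blinding to the hypothesis. The Blinding section claims blinding to allocation, so the defence does not rescue the wording.

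Other parts of the defence stand and limit the point. A reader might infer the following, and the document does not support it:

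- **That the arms differ in the labour CD or in what follows Session 3.** The article describes the labour CD for the trial generally. The Group 2 text is silent on it but does not withhold it. Its reference to a further session repeats the wording of Sessions 1 and 2 and is probably a copying slip. The text needs reconciling; it is not evidence of a difference.
- **That the blinding question has no discriminating power at all.** Some Group 2 women might take a nurse with a CD for a control, and answers could then differ by arm. The sound statement is narrower: the question does not ask which method was received.
- **That the plan overclaims blinding for every self-reported outcome.** For comparisons with usual care the Blinding section already concedes the problem. The overclaim is confined to Group 1 v Group 2.
- **That blinding of data staff fails.** Blinded collection from records and blinded analysis are feasible and nothing contradicts them.

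It is also fair that the firm sentence about the midwife refers to the key secondary outcomes. The same midwife documents the primary outcome, however, and the Abstract makes the firm claim without that limit. When the blinding question should be asked is a matter of preference, since the birth outcome is known at any post-partum form.

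**Conclusion.** The point holds. As described, participants in Groups 1 and 2 are not blinded to the method they receive, so the double-blind label in aim 6 and in the Blinding section is wrong, and the self-reported outcomes in that comparison are not assessed blind. The planned check cannot support the label. The statements about the midwife conflict with each other, and use of a labour CD makes the firmer one unsafe for hypnosis v usual care.

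The size of any bias, and its direction, cannot be obtained from the document. Sample size, randomisation and planned analyses are unaffected. The conclusion assumes that sessions run as described and that women attend; a woman who attends no session and receives posted CDs may know less. The midwife limb further assumes that some women play the labour CD within her hearing. This should be corrected, but it does not invalidate the trial.

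**What to change.** - In aim 6 and the Blinding section, remove the double-blind label. State that participants are not blinded to delivery method, that data abstraction and analysis are blinded, and that the attending midwife may become aware of the allocation.
- Bring Data collection and outcomes and the Abstract into line with that statement.
- Give the blinding item three answers: hypnotherapist-led, CD-led, no hypnosis.
- Record labour-CD use on an existing questionnaire, unless the full data forms already do so.
- Reconcile the Session 3 and labour-CD wording for the two hypnosis arms.

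The cost is a few text edits and one or two reworded items, plus a less favourable blinding claim. Recruitment began in December 2005, so women who have already answered the two-option item would have to be reported separately on that question.
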